### Follow up

At week 16, the subject will be called or will visit the clinic to evaluate for any adverse effects of the drug. For subjects that may discontinue or withdraw early, we will record the rationale on final visit or via telephone conversation and cumulative curcumin dosage at that time point.

Table 2 shows the schedule of activities subjects will undergo in this study from beginning to end. Once the subject complete all phases of the study, indicated in Table 2, they are considered as completed the study.

**Table 2 Tab2:** Schedule of Activities that study subjects will go through from beginning to end

Procedures	Screening Day-7 to -1	Enrollment/baseline Visit 1, Day 1	Study visit 2 Week 4	Study visit 3 Week 8	Study visit 4 Week 12	Follow up Week 16
Informed consent	X					
Demographics	X					
Medical history	X					
Randomization		X				
Administer study intervention		X				
Concomitant medication review	X	X	X	X	X	
Physical exam (including height and weight)	X	X			X	
Vital signs	X	X			X	
ACT Scoring/ Questionnaire		X	X	X	X	
Spirometry (FVC, FEV1)		X	X	X	X	
Blood studies (eosinophils, IgE)		X			X	
Exhaled nitric oxide		X	X	X	X	
INR and PTT		X				
Urine pregnancy test (*if applicable)*		X	X	X	X	
Adverse event review and evaluation		X	X	X	X	X
Complete Forms	X	X	X	X	X	X

*ACT* Asthma control test, *FVC* forced vital capacity, *FEV1* forced expiratory volume in 1 s, *IgE* immunoglobulin E, *INR* international normalized ratio, *PTT* partial thromboplastin time

### Data analysis

Assuming a 30% attrition rate, a sample size of 30 participants is estimated using a moderate effect size for the group x time interaction (f = 0.25 or partial η^2^ = 0.06), level of significance (α = 0.05), and power of 0.80. Effect size was calculated using GPower software (version 3.1.2, University of Dusseldorf, Dusseldorf, Germany).

Data will be summarized using mean and standard deviation for quantitative variables and counts (%) for qualitative variables. The normality of continuous variables will be examined using Shapiro Wilk’s test. The distribution of the participants’ characteristics by study group will be evaluated using chi-square for qualitative variables and independent t- test for quantitative variables. A 2-groupX 4-time points (baseline, week 4, week 8, and week 12) mixed factorial analysis of variance (ANOVA) will be used to examine changes in asthma control test scores, number of days missed from school/work, FEV1 (% predicted), FEV1/FVC ratio, FVC (% predicted), blood eosinophil count, blood total IgE, and FeNO levels by group over time.

There will two main analyses that will be conducted in this study. First: a comparison between study groups will be conducted by looking at group x time interaction effect. The interaction will be evaluated and if there is a statistical significance, an independent t-test will be used by comparing change from baseline between groups at each follow up. A post-hoc Bonferroni test will be conducted for the combined groups if the main effect of time in the mixed factorial found to be significant. Second: A one-way repeated measures, ANOVA, will be used for within-groups to test changes from baseline at each time point. A post hoc testing using Bonferroni test will be used on each group separately if the results of the one-way repeated measures, ANOVA, is found to be statistically significant.

The level of significance will be set at *p* ≤ 0.05. Statistical analysis will be performed using IBM SPSS Software version 25 for Windows (Chicago, IL, USA).

Safety endpoints will be analyzed as summary statistics during treatment. Adverse Events (AEs) will be counted once only for a given participant), presented by severity, frequency, and relationship of AEs with additional information regarding cumulative dosing. Adverse events leading to premature discontinuation from the study intervention and serious treatment-emergent AEs will be presented either in a table or a listing.

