### Design

After screening and meeting inclusion and exclusion criteria, subjects will be randomized 1:1 to one of two arms: (1) placebo (n_1_ = 15) or (2) intervention (n_2_ = 15), curcumin. Once assigned into their group, subjects will receive double-blinded study medication to take daily for 12 weeks. In total, subjects will have up to 6 clinic visits: screening visit (D-7 to -1), a baseline visit (V1), three monthly clinic visits (V2-4) and a follow-up clinic visit or phone-call (week 16).

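### The stated power of 0.80 with 30 participants and 30% attrition rests on an unstated correlation of about 0.55 to 0.60, and the calculation does not fit eosinophils and IgE

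*Protocol article*

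**What the plan says.** The power statement is in the Data analysis section of the protocol article: "Assuming a 30% attrition rate, a sample size of 30 participants is estimated using a moderate effect size for the group x time interaction". The effect size is given as "f = 0.25 or partial η^2^ = 0.06", with "level of significance (α = 0.05" and a target power of 0.80. GPower 3.1.2 is cited for the effect size and SPSS 25 for analysing the data.

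The analysis being powered is "A 2-groupX 4-time points (baseline, week 4, week 8, and week 12) mixed factorial analysis of variance (ANOVA", and the first main analysis is "a comparison between study groups will be conducted by looking at group x time interaction effect". The outcomes listed for this model include blood eosinophil count and total IgE.

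Three other places bear on the figure:
- The Design section says "subjects will be randomized 1:1 to one of two arms", with 15 in each.
- Table 2 schedules the blood studies (eosinophils, IgE) at baseline and week 12 only.
- The Replacements section has subjects replaced if they are randomised but untreated, or if they withdraw or are withdrawn after starting treatment.

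**The concern.** This is the plan's only power claim, and the article calls the study a superiority trial. For a group-by-time interaction, power depends strongly on the correlation between repeated measurements. With 21 completers, a middling correlation leaves power below the stated 0.80.

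The same claim is made to cover outcomes with different numbers of visits. A four-visit calculation cannot describe outcomes measured twice.

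The label moderate also hides how large the targeted difference is: on GPower's default scale, f = 0.25 in this design means that the arms diverge by more than one SD. A reader told that the trial has 80% power for a moderate effect could take a null result as evidence against moderate benefit, which 21 completers cannot provide.

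**Working it through.** **Inputs from the document.** N = 30 randomised, 15 per arm; attrition 30%; k = 2 groups; m = 4 visits; f = 0.25; α = 0.05; target power 0.80.

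**Assumptions, because the document does not give them.** Correlation ρ between visits (0.3 to 0.6 shown, 0.5 as central value); sphericity (ε = 1); GPower's default effect-size scale.

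**Completers.** 30 × 0.7 = 21.

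**Formula.** Noncentral F with df1 = (k−1)(m−1), df2 = (N−k)(m−1) and λ = f²·N·m/(1−ρ). For N = 21 and ρ = 0.5: df1 = 3, df2 = 19 × 3 = 57, λ = 0.0625 × 21 × 4 / 0.5 = 10.5, power 0.752.

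**Reproducing the plan's 30 (four visits).** Completers are the smallest even N with power of at least 0.80; randomised is completers divided by 0.7, rounded up.

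| ρ | Power, 21 completers | Completers for 0.80 | Randomised |
|---|---|---|---|
| 0.3 | 0.59 | 32 | 46 |
| 0.4 | 0.66 | 28 | 40 |
| 0.5 | 0.75 | 24 | 35 (36 for equal arms) |
| 0.55 | 0.80 | 22 | 32 |
| 0.6 | 0.85 | 20 | 29 |

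The stated 30 lies between the last two rows. It is reproduced, to within two patients, only for ρ of about 0.55 to 0.60.

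**Departure from sphericity.** With ε = 0.75, 21 completers give 0.66 at ρ = 0.5, 0.71 at 0.55 and 0.76 at 0.60.

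**Eosinophils and IgE (m = 2).** For N = 21 and ρ = 0.5: df = 1 and 19, λ = 0.0625 × 21 × 2 / 0.5 = 5.25, power 0.585. At ρ = 0.55 it is 0.63, and at 0.60 it is 0.68; 0.80 needs ρ of about 0.70. At ρ = 0.5, 34 completers would be needed. So the correlation that rescues the four-visit figure does not rescue these two outcomes.

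**If replacement restores 30 completers.** At ρ = 0.5, power is 0.90 for four visits and 0.75 for two.

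**What f = 0.25 means in SD units.** With cell effects of ±½(d_t − mean of d_t), f² is their mean square divided by σ². If the arms differ by (0, d, d, d) over the four visits, f = d√3/8, so d = 0.25 × 8/√3 = 1.15 SD. If the difference grows linearly from 0 to d at week 12, f = d√(5/144), so d = 1.34 SD. With two visits, f = d/4, so d = 1.0 SD. None of these depends on ρ.

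**The two effect sizes.** f²/(1 + f²) = 0.0625/1.0625 = 0.0588, which rounds to 0.06. Conversely, √(0.06/0.94) = 0.2526. Under one definition they lead to the same N: 24 completers each on the default scale, 62 each on the SPSS scale (even N). On the SPSS scale, λ = f²(N−k)(m−1) = 0.0625 × 57 = 3.56 for 21 completers, and power is 0.30.

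**The case against.** The strongest reply is that nothing shown contradicts 0.80. Power turns on a correlation that the article does not report, and a condensed article may leave that to the full protocol. At 0.55, 21 completers reach the target; at 0.60, 20 completers suffice and 20/0.7 = 28.6 is close to 30. This stands. A reader might infer that 30 participants simply fail to give 0.80, but the documents do not support that: the shortfall holds at a correlation of 0.5 or below and disappears slightly above it.

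Second, because withdrawals are replaced, 30 randomised need not mean 21 completers. This also stands as a limit on the shortfall. But if replacement restores the numbers, the 30% allowance serves no purpose, so the two sections still need reconciling.

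Third, a reader might infer that f = 0.25 and partial η² = 0.06 contradict each other. They do not; they are the same effect by the usual conversion. A large gap appears only if f is read on GPower's default scale and η² as SPSS reports it, and nothing says that the 0.06 is an SPSS value. What remains is that the option used is not named.

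Fourth, one might guess that attrition was applied by multiplying by 1.3 rather than dividing by 0.7, since 23 × 1.3 = 29.9. That is conjecture. With f = 0.25 and correlation 0.5, 23 completers give 0.796, just below target, and 24 × 1.3 = 31.2.

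Finally, moderate is a conventional label for f = 0.25 and the trial is declared a pilot. That lowers the weight of the point. It does not answer the mismatch for eosinophils and IgE, which needs no assumption to establish.

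**Conclusion.** The point holds in a limited form. The stated 0.80 cannot be verified from the stated inputs. It is consistent with them at a correlation of about 0.55 to 0.60 under sphericity and GPower's default scale, and falls to 0.75 at 0.5 and 0.59 at 0.3.

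The part that rests on the document alone is that the four-time-point calculation cannot apply to eosinophils and IgE. The size of the resulting loss does depend on the correlation, and on holding f at 0.25.

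The tension between the attrition allowance and the replacement rule is also visible in the text itself. This is an inexpensive correction to one power statement in a pilot trial, and no reason to change the number of participants.

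**What to change.** Keep 30 and rewrite the power paragraph:
- State the assumed correlation, the sphericity assumption, the GPower effect-size option, the number of completers and how attrition was applied. For example: with 21 completers, power is 0.75 at correlation 0.5 and 0.80 at 0.55 for four-visit outcomes, and 0.59 to 0.63 for eosinophils and IgE (two visits).
- Give the between-group divergence that f = 0.25 implies: about 1.15 SD if constant from week 4, 1.34 SD if linear to week 12.
- Name eosinophils and IgE as two-time-point outcomes in the analysis.
- Reconcile the 30% allowance with the Replacements section: say whether 30 is the number randomised or the number to complete after replacement.

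The cost is some rewording and a slightly less favourable power figure. No extra patients or visits are needed.

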## Detailed Study procedure

### Baseline

After the subject(s) sign the informed consent, they will undergo history, physical exam including height and weight specifically cardiopulmonary examination, vital signs (blood pressure, heart rate, respiratory rate, and oxygen saturation), and an initial questionnaire that will include current asthma control test and demographics [16, 17]. Subjects will undergo randomization and will then be provided the curcumin or placebo. One member of the study staff will be responsible for randomization but will not share information regarding randomization with the subject nor study staff. Subject will undergo spirometry testing in the clinic site conducted by an experienced respiratory therapist or physician. Effort acceptance criteria is appropriate (American Thoracic Society Grade A—prefer 3 separate efforts with two largest FVC (Forced Vital Capacity) measurements with agreement within 150 mL, and FEV1 (Forced Expiratory Volume in the first second) agreement within 150 mL, B is acceptable if that is the best result after 8 efforts). Spirometer is handheld, and a calibration check will be performed daily with a 3L syringe prior to testing. In addition, Fraction of Exhaled Nitric Oxide (FeNO) will be collected and measured using NIOX VERO® Sensor machines.

Laboratory work will be obtained at the initial visit for plasma eosinophil count and serum total IgE, as well as baseline INR and PTT. Plasma eosinophil count will be drawn in approximately 1.5 mL of blood collected in a lavender top tube. IgE level is minimum 500 µL of blood, although 2 mL is preferred, collected in red tubes (serum) or light green tubes (lithium heparin). Plasma INR/PT and PTT will be collected in 3 mL blue-top tubes. Laboratory specimens will be analyzed via the Loma Linda University Medical Center Clinical Laboratory in compliance with the Clinical Laboratory Improvement Amendments (CLIA) of 1988. Urine pregnancy tests will be conducted for all applicable participants (i.e. females in reproductive age who are not currently on birth control) at baseline, and again at 4, 8 and 12 weeks.

### Visits 2 and 3

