During subsequent visits (Weeks 4, 8), subjects will fill out a questionnaire that includes the Asthma Control Test which evaluates the number of severe asthma exacerbations patient has had including: worsening of symptoms for more than or equal to 48 h of consecutive bronchodilator use, any hospitalizations or emergency room visits [16, 17]. The questionnaire will also evaluate the number of missed days from school or work patient has had from asthma. Subjects will undergo spirometry testing in clinic which will be conducted by an experienced respiratory therapist or physician. Exhaled nitric oxide will be measured at that time as well.

### Visit 4

Subjects will fill out a questionnaire that includes the Asthma Control Test, evaluates the number of severe asthma exacerbations patient has had including worsening of symptoms for more than or equal to 48 h of consecutive bronchodilator use, any hospitalizations or emergency room visits. The questionnaire will also evaluate the number of missed days from school or work patient has had from asthma. Participant will undergo spirometry in clinic which will be conducted by an experienced respiratory therapist or physician. Exhaled nitric oxide will be measured at that time. Laboratory work will be obtained at this initial visit to measure plasma eosinophil count and serum total IgE.

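### Blood eosinophils and total IgE are assigned a four-time-point ANOVA but are measured only at baseline and week 12

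*Protocol article*

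**What the plan says.** The Data analysis section names the model and its time levels: "A 2-groupX 4-time points (baseline, week 4, week 8, and week 12) mixed factorial analysis of variance (ANOVA) will be used". The outcomes assigned to it are asthma control test score, days missed from school or work, FEV1, FEV1/FVC and, at the end of the list, "FVC (% predicted), blood eosinophil count, blood total IgE, and FeNO levels by group over time". That makes eight, two of them blood markers.

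Two further steps rest on the same visits. If the group x time interaction is significant, "an independent t-test will be used by comparing change from baseline between groups at each follow up". Separately, a one-way repeated-measures ANOVA "will be used for within-groups to test changes from baseline at each time point".

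Blood sampling is described in three places:

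- Table 2, in the row beginning "Blood studies (eosinophils, IgE", has marks at Visit 1 (baseline) and Visit 4 (week 12) only.
- The Baseline section says "Laboratory work will be obtained at the initial visit for plasma eosinophil count and serum total IgE".
- The Visit 4 section says "Laboratory work will be obtained at this initial visit to measure plasma eosinophil count and serum total IgE".

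The section on Visits 2 and 3 (weeks 4 and 8) lists the questionnaire and spirometry and adds "Exhaled nitric oxide will be measured at that time as well". It lists no blood draw.

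The sample size paragraph gives one figure, 30 participants. It is based on f = 0.25 for the group x time interaction, alpha 0.05, power 0.80 and 30% attrition.

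**The concern.** The analysis section and the visit schedule disagree. A four-level within-subject factor needs a value at each level, and for eosinophils and IgE two of the four levels are empty by design. Imputation cannot fill them, because no participant has a week 4 or week 8 value from which to impute.

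Two things are at stake. First, the analyst must depart from the written plan for these markers. The candidates (a 2 x 2 ANOVA, a change-score test or a baseline-adjusted comparison, on the raw or a transformed scale) can give different answers. The Dosing and administration section hypothesises an effect on inflammatory biomarkers, so the choice should be settled before data exist. Second, a reader would take the single sample size statement to cover all eight outcomes, when two of them do not have the design it appears to describe.

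**Working it through.** **Structural check.** Measurements scheduled in Table 2 and the visit text:

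| Outcome | Baseline | Week 4 | Week 8 | Week 12 |
|---|---|---|---|---|
| Asthma control test, missed days (questionnaire) | yes | yes | yes | yes |
| Spirometry (FEV1, FVC, FEV1/FVC) | yes | yes | yes | yes |
| FeNO | yes | yes | yes | yes |
| Eosinophils, total IgE | yes | no | no | yes |

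The four-level model fits six of the eight outcomes. For the other two, 0 of 30 participants can have the four values it needs, and up to 30 of 30 can have two. The interaction degrees of freedom at N = 30 are 3 and 84 for the 2 x 4 model, and 1 and 28 for a 2 x 2 model.

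The Visit 4 text refers to an initial visit. Read either way, no blood is drawn at weeks 4 or 8.

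**Power: inputs.** From the Data analysis section: f = 0.25, alpha = 0.05, power 0.80, N = 30 and 30% attrition. From Design: two arms, 1:1. Assumed, because not stated: a common correlation rho between visits, varied from 0.3 to 0.8, and sphericity.

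**Formula.** For the interaction with two groups and m visits, the noncentrality is lambda = f² x N x m / (1 - rho). The F test has m - 1 and (N - 2)(m - 1) degrees of freedom. The required N is the smallest even number with power of at least 0.80.

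**The plan's own figure, m = 4.**

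- At rho = 0.5 and N = 24, lambda = 0.0625 x 24 x 4 / 0.5 = 12 with 3 and 66 df, and power is 0.816. So 24 completers are needed. Dividing by 0.7 gives 35 to enrol; multiplying by 1.3 gives 32.
- At rho = 0.6, 20 completers are needed, and 20 / 0.7 rounds up to 29, or 30 with equal arms.

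The stated 30 is therefore reachable under some unstated correlations and not others. It is neither confirmed nor shown to be wrong, and the present point does not depend on it.

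**Two visits, m = 2.** At rho = 0.5 and N = 34, lambda = 0.0625 x 34 x 2 / 0.5 = 8.5 with 1 and 32 df, and power is 0.807. So 34 completers are needed.

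| Assumed rho | Completers for 0.80, four visits | Completers for 0.80, two visits | Power at 30, two visits | Power at 21, two visits |
|---|---|---|---|---|
| 0.3 | 32 | 46 | 0.608 | 0.452 |
| 0.4 | 28 | 40 | 0.675 | 0.510 |
| 0.5 | 24 | 34 | 0.753 | 0.585 |
| 0.6 | 20 | 28 | 0.840 | 0.681 |
| 0.7 | 16 | 22 | 0.927 | 0.801 |
| 0.8 | 12 | 16 | 0.987 | 0.930 |

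The figure 21 is 30 x 0.7. At every correlation the two-visit requirement exceeds the four-visit one. The comparison holds f fixed; the same f over two and four visits need not be the same treatment effect in the units of the marker.

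**The case against.** The strongest reply is that the plan reduces to something usable without being told to. It fixes the model family, the target (the group x time interaction) and the follow-up contrast (change from baseline). With two draws the mixed ANOVA becomes 2 x 2, its interaction F is the square of the t statistic for the week-12 change, and the within-group ANOVA becomes a paired test. Each follow-up can be read as each follow-up at which the marker was measured. These are also two of eight outcomes in a self-described pilot whose hypothesis concerns exacerbations and asthma control.

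Most of this stands, and it limits the severity. A reader might infer that the two markers have no possible analysis, or that their method will inevitably be picked after the data are seen. The documents do not support that: the natural reduction is available, and a fuller plan that is not shown may state it. What remains is that the article names both the time points and the outcomes. This is a conflict between two stated items, not a detail left out.

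A reader might also infer that the trial is underpowered for these markers. That does not follow. With 21 completers, two-visit power runs from 0.45 to 0.93 over the assumed correlations, and the Replacements section provides for replacing withdrawn participants, so 21 is not settled either.

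Nor do the documents show that analysis on the raw scale would be wrong. They give no distribution for either marker.

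**Conclusion.** The point holds as a mismatch between analysis and schedule, and it should be fixed. For eosinophils and total IgE, two of the eight listed outcomes, the four-level ANOVA has no complete cases. The week 4 and week 8 comparisons attached to it do not exist for these markers. The other six outcomes are unaffected.

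The mismatch itself needs no assumption. The power comparison assumes f = 0.25 for both designs, sphericity and a correlation that the protocol does not give. It supports one conclusion only: a four-visit sample size statement cannot be read as covering outcomes measured twice. It does not show that 30 participants are too few.

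**What to change.** For blood eosinophil count and total IgE, replace the 2 x 4 ANOVA, the t-tests at each follow-up and the within-group repeated-measures ANOVA with one prespecified analysis: a between-group comparison of the week-12 value, adjusted for the baseline value by ANCOVA. State the scale in advance. The log scale is a reasonable option if the markers are expected to be right-skewed.

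A 2 x 2 ANOVA would also remove the contradiction. ANCOVA is preferable because, with equal variances at the two visits, its residual variance relative to the change score is (1 - rho²) / [2(1 - rho)] = (1 + rho)/2. That is 0.65 at rho = 0.3 and 0.90 at rho = 0.8, for the loss of one degree of freedom.

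Add a sentence saying that the sample size statement applies only to outcomes measured at all four visits.

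The cost is wording alone, with no new samples or visits. The Discussion says the study had not been able to take place as scheduled, so when the article was written the change could still have preceded any data.

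### Curcumin is compared with placebo at each visit only after a significant omnibus interaction, and then by change-score t-tests without baseline adjustment: valid, but inefficient

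*Protocol article*

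**What the plan says.** The protocol article (Data analysis) specifies "A 2-groupX 4-time points (baseline, week 4, week 8, and week 12) mixed factorial analysis of variance (ANOVA") for eight outcomes. The first of its two main analyses is between groups: "a comparison between study groups will be conducted by looking at group x time interaction effect". The comparison at individual visits is conditional on that result: "if there is a statistical significance, an independent t-test will be used by comparing change from baseline between groups at each follow up". Baseline enters as one of the four outcome levels and by subtraction, never as a covariate. No visit is singled out as the main one.

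A separate sentence covers time: "A post-hoc Bonferroni test will be conducted for the combined groups if the main effect of time" is significant. The second main analysis is within each arm. Neither of these compares curcumin with placebo.

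The sample size rests on the same interaction: a "moderate effect size for the group x time interaction (f = 0.25 or partial η^2^ = 0.06"), with "level of significance (α = 0.05), and power of 0.80". Table 2 shows the ACT questionnaire, spirometry and FeNO at baseline and at weeks 4, 8 and 12. Eosinophils and IgE are taken at baseline and week 12 only.

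**The concern.** The Methods and design section calls the trial a pilot because little or nothing is known about efficacy. The most useful result of such a trial is an estimate of the treatment difference with its uncertainty. As written, the test between arms at a visit is done only when an omnibus test with 3 degrees of freedom has succeeded, so the differences that get tested are those already selected for being large.

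The follow-up test also uses baseline inefficiently. With 15 per arm, chance imbalance at baseline is likely. Subtracting baseline over-corrects for it whenever the within-person correlation is below 1; a baseline covariate estimates the right amount of correction. At stake are the precision of every between-group estimate and, for some patterns of effect, a substantial amount of power.

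**Working it through.** **1. The plan's own figure.** Inputs from Data analysis: f = 0.25, alpha 0.05, power 0.80, 30% attrition, total 30. From Design: "subjects will be randomized 1:1 to one of two arms", 15 each. The interaction has (2−1)(4−1) = 3 df. For a repeated-measures interaction, λ = N·m·f²/(1−r), with m = 4 and denominator df 3(N−2). The article does not state r.
- r = 0.5: N = 24 (power 0.816); 24/0.7 = 34.3, so 35.
- r = 0.6: N = 20; 20/0.7 = 28.6, so 29.

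The stated 30 is therefore reachable with r near 0.6. It leaves 30 × 0.7 = 21 completers, for whom the interaction test has power 0.752 at r = 0.5 and 0.848 at r = 0.6. Sample size and test agree with each other.

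**2. Precision at one visit.** With equal variances at baseline and follow-up:
- change score: 2(1−r)·SD²
- baseline-adjusted: (1−r²)·SD²
- ratio: (1−r²)/[2(1−r)] = (1+r)/2

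This is 0.65 at r = 0.3, 0.75 at 0.5, 0.85 at 0.7 and 0.90 at 0.8. Estimating the slope in a small trial costs a factor of about 1 + 1/(N−4) = 1 + 1/17 = 1.06 with 21 completers, so the net ratios are about 0.79 at r = 0.5 and 0.90 at r = 0.7. The simulated powers below already include this cost.

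**3. Error under no effect.** In simulation, a significant interaction followed by at least one significant visit occurs in about 4% of trials within an outcome. The three t-tests without the precondition give about 13%.

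**4. Power.** 20,000 simulated trials per case, 11 v 10 completers, equal correlation between visits. The plan is scored as it is written: significant interaction plus a significant t-test at any visit. The comparator is a single week-12 ANCOVA. The maximum effect is 1.0 SD, an assumption. It lies a little below the design effect: f² equals δ²/4 times the mean square of the centred time profile. That gives 3δ²/64 = 0.0625, δ = 1.15 SD, for an effect constant from week 4, and 5δ²/144 = 0.0625, δ = 1.34 SD, for linear onset.

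| Pattern | r | Plan | Week-12 ANCOVA |
|---|---|---|---|
| Linear to 1.0 SD at week 12 | 0.5 | 0.45 | 0.68 |
| 1.0 SD from week 4 | 0.5 | 0.61 | 0.68 |
| 1.0 SD at weeks 4 and 8, 0.5 SD at week 12 | 0.5 | 0.56 | 0.23 |
| Linear | 0.7 | 0.70 | 0.84 |
| From week 4 | 0.7 | 0.85 | 0.84 |
| Waning, as above | 0.7 | 0.81 | 0.32 |
| Linear | 0.8 | 0.88 | 0.94 |
| From week 4 | 0.8 | 0.96 | 0.94 |

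Repeat runs agree within about 0.01. In the first row, an unconditional week-12 change-score t-test has 0.59. So about 14 points of the gap come from the precondition (0.45 to 0.59) and about 9 from the missing covariate (0.59 to 0.68).

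**5. At the protocol's own f = 0.25**, with r = 0.5 and 11 per arm, the interaction has power 0.775, which caps anything conditional on it. Week-12 ANCOVA has 0.92 for linear onset and 0.82 for an effect constant from week 4.

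**The case against.** The strongest defence is that the article treats the interaction itself as the between-group comparison and picks no visit. Scoring the plan on week 12 alone would impose a rule it does not contain. An omnibus test gives up power at any one visit to guard against not knowing when the effect appears, which is reasonable with so little prior data. This stands: the waning rows show the plan well ahead of a single week-12 contrast.

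The figure of 21 completers is also open to question, because the Replacements section has withdrawn subjects replaced. With 15 per arm, r = 0.7 and 1.0 SD, the plan has 0.87 (linear) and 0.95 (from week 4) against 0.95 for ANCOVA. The gap then narrows but does not always close: at r = 0.5 with a linear 0.8 SD effect it is 0.43 v 0.68.

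A reader might infer more than the document supports:
- **That error is inflated, or that sample size and analysis conflict.** Neither is so (steps 1 and 3).
- **That baseline is thrown away.** It is subtracted from every follow-up value. Change-score analysis of a randomised trial is valid, only less efficient.
- **That the pooled time test is the fallback when the interaction fails.** It depends on the main effect of time and is a separate branch.
- **That no treatment difference will be reported after a non-significant interaction.** The article makes the tests conditional, but promises means and SDs without condition. A fuller document may add adjusted estimates.
- **That the 3-df argument covers every outcome.** Eosinophils and IgE have two time points, so their interaction has 1 df and is equivalent to the change-score t-test. Only the covariate argument applies to them.

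**Conclusion.** The concern holds as one of efficiency and of a contrast made conditional on a p-value. It is not one of validity. The loss of precision at a visit is firm in direction: (1+r)/2 of the change-score variance, 25% lower at r = 0.5 and 15% lower at r = 0.7, slightly less after the small-sample cost.

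The effect on power is conditional. Against week-12 ANCOVA it ranges from about 23 points lost (linear onset, r = 0.5), through no loss (effect from week 4, r = 0.7), to a clear advantage for the plan if the effect wanes. A general claim that the plan loses power is not supported. The correlation, the 1.0 SD effect, the onset patterns and equal correlation between visits are all assumptions; the article gives none of them. The change is worth making because it costs almost nothing.

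**What to change.** For the outcomes measured at all four visits, replace the conditional change-score t-tests with one model of the values at weeks 4, 8 and 12, with group, visit, group by visit, baseline and baseline by visit as fixed effects and allowance for within-subject correlation. Report the baseline-adjusted group difference with 95% CI at every visit, whether or not the interaction is significant.

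Within each outcome, name one contrast in advance as the main one (for example week 12, the end of treatment) and label the others supportive. Removing the precondition without doing this would raise the chance of some false-positive visit from about 4% to about 13%. If an early or waning effect is thought plausible, weigh that when choosing the contrast. The omnibus group by visit test can stay as a supportive test.

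For eosinophils and IgE, use ANCOVA of the week-12 value on baseline.

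The cost is a change of wording, one different model procedure, and one or two degrees of freedom for the baseline covariate. No visits, data or patients are added. The Discussion says that the study had not yet been able to take place, so the change could be made before any outcome data are seen.
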